## Background

Esophageal cancer resulted in 7,606 deaths in the United Kingdom in 2008, reflecting a 70% increase in male age-standardized mortality rates compared to 1971. It is the sixth most common cause of cancer deaths (fourth in men) and incidence rates are increasing by 4.2% per annum [1]. Prognosis is poor, with five-year survival rates of 10 to 15% [2]. It is predominately a disease of the elderly, with prevalence highest in the seventh and eighth decades of life. Most patients present with incurable disease, and for advanced disease, mean survival is three to five months [3].

The emphasis of treatment for the majority of patients is therefore on effective palliative interventions, with 70 to 90% requiring intervention for dysphagia [4, 5]. This single symptom has profound impact on social and physical functioning and other aspects of quality of life (QoL). Interventions to improve swallowing must therefore aim to produce prompt and lasting palliation of dysphagia whilst minimizing the need for late re-interventions and hospitalization. Interventions must produce these benefits without causing significant impairment of other aspects of QoL.

The most recent Cochrane systematic review [6] of interventions for dysphagia in esophageal cancer confirms the efficacy of self-expanding metal stents (SEMS) in providing rapid initial relief of dysphagia, with fewer adverse effects and lower re-intervention rates than endoscopic ablative therapies.

A health technology assessment (HTA) [7] also highlights the efficacy of stent placement. However, delayed complications are common and result in later re-interventions. A pragmatic study as part of that assessment found that 35% of patients receiving stents required re-interventions [8]. Homs *et al.*
[9] in a comparative study of brachytherapy described a hemorrhage rate of 13% in patients treated with a stent within a median of 123 days post-insertion. Conio *et al*. [10] in a randomized comparison of two stent types described tumor overgrowth in 19% within a median of 97 days post-insertion.

It is such late re-interventions and complications which account for the major proportion of dysphagia treatment costs [8], requiring travel to hospital and inpatient stays which also impair QoL. This is consistent with estimations that healthcare costs in general in the last year of life account for 20 to 30% of overall healthcare budgets [11].

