### Assessments and outcomes

A research practitioner will collect baseline data prior to stent insertion, one week following stent insertion, four weeks post stent insertion (and after radiotherapy in the intervention arm) and four-weekly thereafter until death. Dedicated research staff will visit patients at home or a place of their choice and the patients will be asked to complete the questionnaires themselves whenever possible.

The assessments at baseline will be measured using WHO performance status, QoL questionnaires (European Organisation for Research and Treatment of Cancer Quality of Life Questionnaire C30(EORTC QLQ-C30), EORTC QLQ-OG25, EuroQuol-5D (EQ-5D)) and the toxicity assessment Common terminology Criteria for Adverse Events (CTCAE) v4.03.

The assessment performed within one week of stent insertion will be measured using WHO performance status, questionnaires (EORTC QLQ-C30, EORTC QLQ-OG25, EQ-5D), the toxicity assessment (CTCAE v4.03), stent morbidity data, and a qualitative interview (subset of patients).

The assessments performed four weeks after stent insertion and four-weekly thereafter until death will be measured using the WHO performance status, questionnaires (EORTC QLQ-C30, EORTC QLQ-OG25, EQ-5D), the toxicity assessment (CTCAE v4.03), stent morbidity data, qualitative interview (subset of participants, week four and week eight only).

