#### Morbidity

Overall length of hospital stay, complication rates, number of blood transfusions, and re-intervention rates will be gathered from case notes and captured in the case report forms. Early complications will be defined as those occurring within seven days of the intervention, and late complications will be defined as those occurring more than seven days after the intervention. Standard definitions of stent complications will be clearly described in the protocol.

Toxicity data will be scored using the National Cancer Institute CTCAE v4.03 and the Radiation Therapy Oncology Group acute/late questionnaire at baseline, during treatment, and at the pre-specified time points on follow-up. SAEs will be monitored in real-time by the chief investigator and trial management group (TMG.) Data will also be collected on symptom burden including pain, eating restrictions, and physical functioning via the EORTC QLQ-C30 and QLQ-OG25 scales.

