### Sample size considerations

In a population with a median survival of approximately four months, an increase in median time to deterioration in self-reported dysphagia of four weeks is considered clinically meaningful. This is based on previous results in Homs *et al*. [9] and expert multidisciplinary and service user opinion. A survey of participating centers demonstrated clinician accord with this. Time to event will be calculated from the time of stent insertion to the time of deterioration (of 11 points or more) or death. Sample size is therefore based on a time to event analysis, to detect an increase in median time to deterioration in self-reported dysphagia of four weeks: from 12 to 16 weeks (equivalent to a hazard ratio (HR) of 0.75 and a difference in 12-week event rate of 50 versus 60%). Recruitment time will be 4.25 years with a six-month follow-up after the final patient is recruited. For 80% power with an alpha of 0.05 based on a two-sided log rank test, 198 patients per arm will be required, with 396 in total, which is a total of 384 events. Assuming 20% attrition, a total of 496 patients will be required. The degree of attrition is set at this higher level because of the vulnerability of the patient population.

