### Statistical analysis

All analyses will be performed on a full intention-to-treat basis, that is, all patients randomized will be included, and all patients will be analyzed according to their allocated group whatever treatment they receive. Descriptive statistics of the patient characteristics within each treatment group will be presented (including a summary of the type of the treatment each patient actual received).

The main analysis will compare the time until self-reported dysphagia progression between the two groups using Kaplan-Meier curves and the log-rank test. The final analysis will take place when 384 events (deterioration or deaths) have been reported, which is expected to be approximately six months after accrual closes. Kaplan-Meier curves and log-rank tests will also be used to compare the two groups on the secondary outcomes of overall survival. It is possible the data for the secondary endpoints (such as toxicity) may be mature enough for analysis and presentation before the main overall survival primary endpoint. The secondary outcomes of proportions of morbidities and re-intervention rates will be compared using a chi-square test. The area under the curve of HRQoL scores will be compared using t-tests adjusted for follow-up interval and survival. The main analysis will be carried out when the required number of events has been reached (see proposed sample size above).

No formal subgroup analyses are planned to look at differences in primary and secondary endpoints between treatment groups within specific groupings based on patient characteristics. However exploratory analysis will be conducted to explore whether there is any consistent benefit from using radiotherapy after a stent in different subgroups by creating HR plots and carrying out tests for interaction or trend based on chi-square analysis. The statistical package STATA (StataCorp LP, Texas, USA) will be used for all analysis and a statistical analysis plan will be written before the data is analyzed.

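### The chi-square comparison of re-interventions and late complications has no time window or survival adjustment, so it mixes the effect on these events with any effect on survival

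*Protocol article*

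**What the plan says.** The test is named in the Statistical analysis section of the protocol article: "The secondary outcomes of proportions of morbidities and re-intervention rates will be compared using a chi-square test". The sentence gives no period of observation, person-time denominator or adjustment.

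The Assessments and outcomes section schedules stent morbidity data "four-weekly thereafter until death". Under Morbidity, "complication rates, number of blood transfusions, and re-intervention rates will be gathered from case notes", with no cut-off date. That section fixes a window for one class of event only: "Early complications will be defined as those occurring within seven days of the intervention". The other class is open-ended: "late complications will be defined as those occurring more than seven days after the intervention".

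The Abstract and the Background both raise the possibility that radiotherapy lengthens survival. The Statistical analysis section plans to allow for follow-up length and survival when it compares area under the curve for quality of life. It makes no such allowance for re-intervention or morbidity.

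**The concern.** A chi-square test on patients with and without an event suits a risk period of equal length in both arms. Here the risk period for a re-intervention or late complication ends at death. If one arm lives longer, its patients have more time in which a stent can fail. The proportion ever re-intervened then responds to two effects at once: the weekly hazard of re-intervention while alive, and the length of life.

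This matters because the Background presents late re-interventions and complications as the main source of dysphagia treatment cost and a burden on patients, and gives their reduction as a reason for the trial. The trial hopes for fewer re-interventions and allows for longer survival. Under the named test, the second can cancel the first or reverse its apparent direction. An ever/never count also discards repeat re-interventions.

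**Working it through.** **The plan's own figures.** The article gives no power or sample size for re-intervention or morbidity, so there is no figure on this point to reproduce. The primary sample size is sound and not at issue: Freedman's formula for a hazard ratio (HR) of 0.75, 80% power and two-sided 5% gives 385 events, against 384 stated.

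**Inputs from the article**
- Control re-intervention, from the Background: "35% of patients receiving stents required re-interventions".
- Survival, from Sample size considerations: "In a population with a median survival of approximately four months", taken as 17.4 weeks.
- 496 patients randomized 1:1, so 248 per arm; 4.25 years of accrual and six months of further follow-up.

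**Assumptions, not in the article:** constant hazards; 35% read as the probability of re-intervention before death; HRs for death and for re-intervention as listed below.

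**Formula.** With weekly hazards r (first re-intervention) and d (death) and follow-up to death,

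P(ever re-intervened) = r / (r + d).

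The odds of being re-intervened are r/d, so the odds ratio between arms is HR(re-intervention) / HR(death). The longer-living arm looks worse if its re-intervention hazard falls by less than its death hazard. It looks the same if both fall equally. If the re-intervention hazard falls by more, the benefit shows but is diluted.

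**Control arm.** d = ln 2 / 17.4 = 0.0398 per week. r = d × 0.35/0.65 = 0.0215 per week.

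**Four-week gain in median survival, re-intervention hazard unchanged.** d = ln 2 / 21.4 = 0.0324, a death HR of 17.4/21.4 = 0.81. P = 0.0215 / (0.0215 + 0.0324) = 39.8%. A re-intervention HR of 0.81 would bring this back to 35%, so under this gain a true 19% reduction would be invisible.

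**Other combinations, control 35%**

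| HR death | HR re-intervention | Radiotherapy arm |
|---|---|---|
| 1.00 | 0.75 | 28.8% |
| 0.85 | 0.75 | 32.2% |
| 0.75 | 0.75 | 35.0% |
| 0.67 | 0.75 | 37.6% |
| 0.75 | 1.00 | 41.8% |

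The same 25% reduction in hazard runs from a 6-point benefit to an apparent 3-point harm as the assumed survival effect grows. With the re-intervention hazard unchanged and a death HR of 0.75, a control proportion of 20% becomes 25.0%, and 50% becomes 57.1%.

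**Simulation.** 4,000 trials per scenario, 248 per arm, with the stated accrual and follow-up:
- Death HR 0.75, re-intervention hazard unchanged: 34.5% versus 40.8%. The chi-square is significant against radiotherapy in 30% of trials.
- Both HRs 0.75: 34.5% versus 34.0%. The chi-square favours radiotherapy in about 4% of trials; a cause-specific log-rank test that censors at death does so in 45%.
- Death HR 1.00, re-intervention HR 0.75: the chi-square favours radiotherapy in 32%, the cause-specific log-rank in 43%.

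**The case against.** The strongest objection is that the distortion is conditional. A reader might infer that an arm with longer survival must look worse. The documents do not support that. They call a survival benefit possible and state no size for it, and even with one the direction depends on which hazard falls further. The four-week gain used above equals the trial's dysphagia target; it is an assumption, not a survival target of the trial. In that scenario the usual chi-square result is non-significance: the 4.8-point difference has a standard error of about 0.043 with 248 per arm, z is about 1.1, and significance against radiotherapy would occur in roughly 20% of trials. All of this stands and limits the point.

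The article also never says outright that the compared proportions accumulate until death. The full protocol or the analysis plan may set a window. That tempers certainty, but the article names the test and sets it beside follow-up to death and an open-ended late category.

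A reader might infer that all morbidity is affected. It is not: early complications have a seven-day window. Nor is neglect of censoring a serious charge. With survival this short and analysis about six months after accrual closes, nearly all patients are observed to death, and in the simulation administrative censoring moved the proportions by about one point or less.

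The crude proportion is also a legitimate description of total patient burden. The economic case does not hang on this test, because the Cost effectiveness section analyses total resource use separately. Both are true. Neither makes the chi-square a test of whether radiotherapy lowers the re-intervention hazard.

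**Conclusion.** The point holds in conditional form. For re-interventions and late complications, the named comparison cannot separate an effect on the event from an effect on survival. If survival is equal, there is no such distortion. If survival differs, the observed odds ratio is the re-intervention HR divided by the death HR, under constant hazards and follow-up to death. With 35% in control, an unchanged re-intervention hazard then shows as 39.8% (death HR 0.81) or 41.8% (death HR 0.75), and equal reductions in both hazards show as no difference at all. The HRs and constant hazards are assumptions; the 35% and the four-month median come from the article. The affected outcomes are secondary.

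**What to change.** For re-interventions and late complications only, replace the chi-square as the main comparison with one of these:

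- a cause-specific HR for time to first event, censoring at death; or
- a rate per patient-week alive, by Poisson or negative binomial regression with log time alive as offset, which also uses repeat events.

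Beside it, report the cumulative incidence with death as a competing event, or the crude proportion, as a measure of total burden. Say plainly that this measure still responds to survival. Gray's test is no cure: under the model above the cumulative incidence is [r/(r + d)] × [1 − exp(−(r + d)t)], which is higher at every t > 0 when d falls and r does not, and which levels off at the same 39.8% in the four-week example. Keep the chi-square for complications within seven days.

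The cost is a change of wording before the data are analysed, some extra analysis, and reliance on event dates from case notes. Classing complications as early or late already needs event timing, and dates of death are collected for overall survival. No change to the primary analysis or the sample size is needed.

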**Methods/Design:**

The study is a randomized multicenter phase III trial, with an internal pilot phase, comparing stent alone versus stent plus palliative radiotherapy in patients with incurable esophageal cancer. Eligible participants are those with advanced esophageal cancer who are in need of stent insertion for primary management of dysphagia. Radiotherapy will be administered as 20 Gray (Gy) in five fractions over one week or 30 Gy in 10 fractions over two weeks, within four weeks of stent insertion. The internal pilot will assess rates and methods of recruitment; pre-agreed criteria will determine progression to the main trial. In total, 496 patients will be randomized in a 1:1 ratio with follow up until death. The primary outcome is time to progression of patient-reported dysphagia. Secondary outcomes include survival, toxicity, health resource utilization, and quality of life. An embedded qualitative study will explore the feasibility of patient recruitment by examining patients’ motivations for involvement and their experiences of consent and recruitment, including reasons for not consenting. It will also explore patients’ experiences of each trial arm.

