Of the non-stent interventions, brachytherapy studies [9, 12] suggest this treatment gives longer dysphagia-free survival and more stable QoL compared to a stent. However, a recent survey by the Royal College of Radiologists (London, United Kingdom) showed that brachytherapy treatment for all tumor sites accounts for only 2.5% of all radiotherapy patients. There is little access to, or expertise in, this type of radiotherapy for esophageal cancer patients in the United Kingdom [13]. In contrast, external beam radiotherapy is readily accessible by patients at regional cancer centers across the United Kingdom, although its use in the immediate post-stent period has not been rigorously studied and is not routinely used.

Available evidence therefore suggests that a stent is an appropriate intervention for rapid dysphagia relief in incurable esophageal cancer. The efficacy of stent alone, however, is limited by early problems with pain, decline in general aspects of QoL, and later complications such as hemorrhage and tumor overgrowth. Re-interventions not only impose significant burden on NHS resources but decrease the QoL and functioning of an unwell, predominantly elderly, population. Combination with other treatments might reduce costs and patient burden; for example the addition of radiotherapy may ameliorate these problems and provide additional survival benefit.

Given the sporadic and consistently limited availability of brachytherapy in the United Kingdom, the overarching aim of this study is to address uncertainties in the current evidence base by assessing whether the addition of external beam radiotherapy prolongs improvement in dysphagia, improves QoL, and reduces health economic and personal burden in patients undergoing stent placement.

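### Late complications and re-interventions are compared as crude proportions although follow-up ends at death, so a survival gain from radiotherapy would attenuate, and could mask or reverse, a true fall in their rate

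*Protocol article*

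**What the plan says.** In the protocol article, the Statistical analysis section names the test: "The secondary outcomes of proportions of morbidities and re-intervention rates will be compared using a chi-square test". It gives no time window and no allowance for time at risk or death.

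Four other statements bear on it:

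- **Window.** Under Morbidity, "late complications will be defined as those occurring more than seven days after the intervention". There is no upper limit.
- **Follow-up.** The abstract says: "In total, 496 patients will be randomized in a 1:1 ratio with follow up until death".
- **Timing.** The Background cites one stent study that "described a hemorrhage rate of 13% in patients treated with a stent within a median of 123 days post-insertion" and another that "described tumor overgrowth in 19% within a median of 97 days post-insertion". It also cites a 35% re-intervention rate after stenting. Sample size considerations begins: "In a population with a median survival of approximately four months".
- **Hypothesis.** The Background says of late complications and re-interventions that "the addition of radiotherapy may ameliorate these problems and provide additional survival benefit".

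The same Statistical analysis section does allow for survival elsewhere: "The area under the curve of HRQoL scores will be compared using t-tests adjusted for follow-up interval and survival".

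**The concern.** A chi-square test on whether a patient ever had a late event counts someone who died event-free in week 3 the same as someone who lived a year without one. The cited late events arise at about 97 and 123 days, close to the median survival of about four months (122 days). Whether a patient is ever recorded with one therefore depends on length of life as well as on the complication rate.

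This would matter little if survival were expected to be equal in the two arms. The article hypothesizes that radiotherapy may both reduce late problems and lengthen life. In the crude proportion those two benefits work against each other: longer life means more time in which to bleed, obstruct or need re-intervention. Fewer late complications and re-interventions is part of the stated reason for adding radiotherapy, so the planned comparison answers that question least well if radiotherapy also extends life.

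**Working it through.** **The plan's own figures.** The article gives no power or sample size for these chi-square comparisons, so there is none to reproduce. The number per arm follows from Sample size considerations: 198 / 0.8 = 247.5, rounded up to 248, and 2 × 248 = 496, as stated.

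**Inputs from the article.** Median survival is about four months, or 17.4 weeks. Control proportions are 13% (hemorrhage), 19% (overgrowth) and 35% (re-intervention).

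**Assumptions not in the article.** Hazards are constant. The death hazard ratio (HRd) and the complication hazard ratio (HRc) are varied.

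**Model.** With control death hazard μ = ln2 / 17.4 per week and control complication hazard λ, the proportion who ever have an event before death is:

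- control: p0 = λ / (λ + μ)
- radiotherapy: p1 = λ·HRc / (λ·HRc + μ·HRd)

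Setting p0 to the cited figure gives p1 = p0·HRc / (p0·HRc + (1 − p0)·HRd). The crude odds ratio is then exactly HRc / HRd. So the chi-square test asks whether the complication hazard fell proportionally more than the death hazard, not whether it fell.

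**Plausibility of constant hazards.** The model puts the median time to an observed complication at 17.4 × (1 − p0) weeks. That is 14.1 weeks (99 days) at 19% and 15.1 weeks (106 days) at 13%, against the cited 97 and 123 days. The agreement is rough but adequate for an illustration.

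**Proportions.**

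| HRd | HRc | Control 13% | Control 19% |
|---|---|---|---|
| 0.8 | 1 | 0.13 / (0.13 + 0.696) = 15.7% | 0.19 / (0.19 + 0.648) = 22.7% |
| 0.8 | 0.75 | 0.0975 / (0.0975 + 0.696) = 12.3% | 0.1425 / (0.1425 + 0.648) = 18.0% |
| 0.75 | 0.75 | 13.0% | 19.0% |
| 0.7 | 0.75 | 0.0975 / (0.0975 + 0.609) = 13.8% | 0.1425 / (0.1425 + 0.567) = 20.1% |
| 0.9 | 0.6 | 0.078 / (0.078 + 0.783) = 9.1% | 0.114 / (0.114 + 0.729) = 13.5% |

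A true 25% fall therefore shows as a risk ratio of about 0.95 at HRd 0.8, 1.00 at HRd 0.75 and 1.06 at HRd 0.7. In the last row, a large fall with a small survival gain keeps its direction, with a risk ratio of about 0.70.

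**Rejection rates** (simulation, 4,000 trials per scenario, 248 per arm, two-sided 5%):

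- Complication hazard unchanged, HRd 0.8: chi-square rejects in about 13% of trials (13% control rate) and 16% (19% control rate), nearly always as apparent harm. At HRd 0.9 it rejects in about 7% and 7.5%. The cause-specific log-rank test stays at 5%.
- True 40% fall, HRd 0.8: chi-square power is about 18% (13% control rate) and 23% (19%), against about 49% and 65% for the cause-specific log-rank test.
- True 25% fall, HRd 0.8: the log-rank test has only about 21% (13%) and 28% (19%) power.
- Re-intervention at 35%, true 25% fall: at HRd 0.8 chi-square rejects in about 7% of trials and log-rank in about 46%. At HRd 0.9 the figures are about 17% and 44%. With no survival gain they are about 32% and 44%.

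**The case against.** Several points on the other side stand.

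- **Size depends on an assumed survival effect.** The article says only that radiotherapy may extend life. The hazard ratio of 0.75 in Sample size considerations is for dysphagia deterioration or death and cannot be read as a survival hazard ratio. At a death hazard ratio of 0.9 the rejection rate under an unchanged hazard is close to nominal.
- **The crude proportion is a legitimate quantity.** With follow-up to death it is lifetime risk, which is relevant to patient and NHS burden. On that reading 13% v 15.7% is a real difference and the extra rejections are not errors. They become errors only if read as a higher complication rate. Cumulative incidence over the whole of follow-up would give nearly the same answer as the chi-square test.
- **The alternative test is not powerful for a modest effect.** For a 25% fall at the 13% and 19% control rates, most trials would be non-significant under either test. That the log-rank test held 5% also follows from simulating independent hazards.
- **The consequence is contained.** These are secondary outcomes. Survival is tested separately and would be visible beside them, and the primary analysis is untouched.

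A reader might infer that any survival gain hides or reverses a reduction. The model does not support that: smaller gains only attenuate it. A reader might also infer that the planned test would usually report a false excess, but even at a death hazard ratio of 0.8 about 85% of trials would not.

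What remains is that the article names a test for a rate question that it cannot separate from survival, while allowing for survival in the quality-of-life comparison. The early/late split does not equalize exposure.

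**Conclusion.** The point holds in a conditional form. The planned chi-square comparison mixes the complication rate with time alive. If radiotherapy prolongs survival, it attenuates a true fall in late complications and re-interventions. It masks the fall when the proportional cut in the death hazard equals the cut in the complication hazard, and reverses it when the cut in the death hazard is larger. Without a survival gain there is no such distortion.

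The size rests on constant hazards, control rates taken from the Background, and a death hazard ratio that the documents do not give. Over the range 0.7 to 0.9, a true 25% fall at the 13% and 19% control rates appears as a risk ratio from about 1.06 to about 0.86 (at 0.9: 0.0975 / (0.0975 + 0.783) = 11.1% and 0.1425 / (0.1425 + 0.729) = 16.4%). With no survival gain it would be about 0.78 (0.0975 / (0.0975 + 0.87) = 10.1% and 0.1425 / (0.1425 + 0.81) = 15.0%).

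Early complications, within seven days, are barely affected. The change is worth making because it is cheap and bears on the trial's own rationale.

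**What to change.** For late complications and re-interventions, make the main comparison the cause-specific hazard of the first event, by log-rank test or Cox model, censoring at death.

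- **Time origin.** Count time from stent insertion, as Sample size considerations does for the primary outcome. Randomization is unsuitable because it precedes stent insertion.
- **Start of risk.** For late complications, start the risk period after day 7, by landmark or delayed entry, because no late event can occur before then. This takes the intervention in the Morbidity definition to be the stent.
- **Display.** Show cumulative incidence by arm with death as the competing event. It should accompany the hazard comparison, not replace it, since over full follow-up it nearly reproduces the crude result.
- **Keep.** Report the crude proportion as a descriptive lifetime risk, and keep the chi-square test for early complications.

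The cost is a wording change in the protocol and analysis plan, plus one extra analysis and display. Event timing is already needed to separate early from late complications, and dates of death are collected for overall survival. The downside is that the hazard result must be read beside the lifetime risk: a lower complication rate and an unchanged or higher lifetime risk can both be true.
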